**FIGURE 1 F1:**
[figure not shown]
Schematic overview of SAMPLE-PE study design and evaluation components.

**FIGURE 2 F2:**
[figure not shown]
SPIRIT participant timeline.

### Sample Size and Statistical Power

Based on previous studies (Morgan et al., 2013), we anticipate a small to medium effect size of *d* = 0.4 for changes in movement competence. In accordance with CONSORT guidelines (Schulz et al., 2020) our power calculations were adjusted for the clustering of effects at the class level. Adjusting for clustering at class level, we used a correction factor of [1+(m-1) × ICC], with participants m per class and the intraclass correlation ICC coefficient. Assuming an average class size of about 20 participants and an ICC for movement competence of 0.16 [based on TGMD-2 data of 8 classes from 7 to 8 year-olds (Rudd et al., 2016), the correction factor is 4.04 (i.e., 1+(20-1) × 0.16) (Lubans et al., 2016)]. The power calculation to detect within-between interactions for three groups and across three time points with 90% power, α levels set at *p* < 0.05 and *r* = 0.5 suggested a minimal sample size of 54 children. The final power calculation including the correction factor indicated sample size of 218 children. Allowing for 20% dropout at each time points (Foulkes et al., 2017), the aim of this study will be to have a sample of at least 314 children.

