## Methods

### Design

A cluster-RCT will be conducted to evaluate the efficacy of the SAMPLE-PE pedagogy interventions that aim to improve movement competence and other key aspects of children’s holistic development in year 1 children (5–6 years) in 12 government-funded primary schools. The trial has received institutional research ethics committee approval (Reference 17/SPS/031), and is registered (ClinicalTrials.gov identifier: NCT03551366). A schematic overview of the intervention and evaluation components is shown in Figure 1, while the flow diagram of schools through the study is shown in Figure 2. The UK school academic calendar spans September to the middle of July. Data collection will occur over 14 months with measurements at baseline (T0, January–February, 2018) and post-intervention (T1, June–July, 2018), whilst children are in year 1 of primary school, with a follow-up planned for 6 months after the intervention has finished (T2, January–February, 2019; year 2 of primary school; 1 year post-baseline assessments). The design, conduct and reporting of this cluster RCT will adhere to the Consolidated Standards of Reporting Trials (CONSORT) guidelines for group trials (Schulz et al., 2020) and the Standard Protocol Items: Recommendations for Interventions (SPIRIT) checklist (Supplementary File 4) (Chan et al., 2013).

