### Blinding and Randomization

For practical reasons, it will not be possible to blind the researchers, teachers, and coaches to group allocation. Following collection of headteacher consent, randomization will take place at the school (cluster) level. Schools will then be matched based on the number of students enrolled and level of deprivation identified using the school postcode (Ministry of Housing Communities Local Government, 2018). Following this, schools will be randomly allocated to an intervention condition or control group using a computer-based random number producing algorithm by an independent researcher not associated with the study. This method ensures that schools had an equal chance of allocation to each group.

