#### Control (*n* = 6 Schools)

Control schools will be asked to continue with their usual PE curriculum provision, and timetable and deliver 2 × 60 min PE lessons per week for 15 weeks. The control schools follow current national curriculum aims for PE in Key Stage 1 (early primary), which state that: *‘Pupils should develop fundamental movement skills, become increasingly competent and confident and access a broad range of opportunities to extend their agility, balance and coordination, individually and with others. They should be able to engage in competitive (both against self and against others) and co-operative physical activities, in a range of increasingly challenging situations’* (Department for Education, 2013). Information pertaining to the PE curriculum being delivered in control schools will be collected as part of a process evaluation (described later in secondary outcomes).

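### The 90% power at d = 0.4 belongs to an omnibus interaction test with child-level degrees of freedom; the pairwise contrasts among 12 randomised schools do not reach it at 218 analysed

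*Protocol article*

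**What the plan says.** Protocol article, Sample Size and Statistical Power:

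- Effect: "we anticipate a small to medium effect size of *d* = 0.4 for changes in movement competence".
- Clustering: "our power calculations were adjusted for the clustering of effects at the class level". The inputs are given as "Assuming an average class size of about 20 participants and an ICC for movement competence of 0.16", so that "the correction factor is 4.04 (i.e., 1+(20-1) × 0.16".
- Test: a within-between interaction "for three groups and across three time points with 90% power, α levels set at *p* < 0.05 and *r* = 0.5". This gives 54 children, 218 after the correction factor and 314 after dropout.

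Elsewhere in the same article:

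- Blinding and Randomization: "randomization will take place at the school (cluster) level".
- Design: the trial is run "in 12 government-funded primary schools".
- The control section is headed "Control (*n* = 6 Schools)", which leaves six schools for two pedagogy arms. Their split is not stated.
- Hypotheses: each pedagogy is expected to do better than usual PE on movement competence. Non-linear is expected to exceed Linear on creativity and fall below it on technical proficiency.
- Data Analysis: mixed models with 0/1-coded group variables, whose coefficients are also pairwise comparisons.

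The number of schools, the allocation and the pairwise contrasts do not enter the power calculation.

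**The concern.** Schools are randomised, so arm differences have to be judged against variation between schools. With 12 schools and three arms, 12 - 3 = 9 degrees of freedom are available. The calculation instead uses a 4-df interaction F test with about a hundred child-level denominator degrees of freedom, then multiplies the answer by a class-level factor. It also answers a different question from the hypotheses: an omnibus interaction test can be adequately powered when no single pairwise contrast is.

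The risk is in interpretation. A reader who believes the 90% will take a null result on the primary outcome as evidence against a pedagogy, when the contrast concerned may have had well under 90% power at the planned effect.

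**Working it through.** **1. The plan's own figure.** For the interaction F test, λ = f²·N·T/(1 - r), with df (k - 1)(T - 1) and (N - k)(T - 1). Inputs from the article: k = 3 groups, T = 3 times, r = 0.5, α = 0.05. The article gives no f; f = d/2 = 0.2 is assumed.

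- N = 54: λ = 0.04 × 54 × 3/0.5 = 12.96, df 4 and 102, power 81.6%.
- N = 67: λ = 16.08, power 90.2%. N = 66 gives 89.7%.
- 54 × 4.04 = 218.2 reproduces the 218.

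So the clustering step reproduces, but 54 does not give 90% for the test described.

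**2. Effect-size conversion.** If d = 0.4 means a 0.4 SD gain in both pedagogy arms at T1 and T2 with equal groups, f² = 0.16 × (2/9) × (2/9) = 0.0079, so f = 0.089. With 6/3/3 weights, f = 0.094. At 54 effective children the interaction test then has 20-23% power.

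**3. Pairwise contrasts at school level.** Assumptions: 3/3/6 schools of equal size; m = 218/12 = 18.2; outcome SD 1; total correlation between any two time points r = 0.5; two-sided 5% t test on 9 df. Write ρ for the school ICC and a for the correlation over time of a school's true mean.

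- Variance of a school mean: V = ρ + (1 - ρ)/m. At ρ = 0.16: 0.16 + 0.84/18.2 = 0.206.
- Covariance between times: C = ρa + (0.5 - ρa)/m. At ρ = 0.16: 0.1485 for a = 0.8 and 0.1787 for a = 1.0.
- Baseline-adjusted, one follow-up: V - C²/V = 0.0993 (a = 0.8) or 0.0514 (a = 1.0).
- Baseline-adjusted, T1 and T2 averaged: (V + C)/2 - C²/V = 0.0705 or 0.0376.
- SE = √[variance × (1/n₁ + 1/n₂)]. The bracket is 1/3 + 1/6 = 1/2 for pedagogy versus control and 1/3 + 1/3 = 2/3 for Linear versus Non-linear.

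For pedagogy versus control at ρ = 0.16 the SEs are 0.321 (unadjusted), 0.223 to 0.160 (one follow-up) and 0.188 to 0.137 (averaged).

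Power at d = 0.4, ranges over a = 0.8 to 1.0:

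| School ICC | Contrast | No baseline | One follow-up | T1 and T2 averaged |
|---|---|---|---|---|
| 0.16 | Pedagogy v control | 20% | 36-60% | 48-74% |
| 0.16 | Linear v Non-linear | 16% | 28-49% | 38-61% |
| 0.05 | Pedagogy v control | 35% | 54-64% | 69-78% |
| 0 | Pedagogy v control | 58% | 70% | 86% |

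The article does not assign d = 0.4 to Linear versus Non-linear; those rows assume it.

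**4. Detectable difference at 90%.** On 9 df this is about 3.65 SE. At ρ = 0.16 it runs from 3.65 × 0.137 = 0.50 to 3.65 × 0.321 = 1.17 SD for pedagogy versus control. For Linear versus Non-linear (SE 0.158 to 0.371) it runs from about 0.6 to 1.35 SD.

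**5. What drives the shortfall.**

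- Level of clustering: with 18.2 children per school the design effect is 1 + 17.2 × 0.16 = 3.75. With all 314 (26.2 per school) it is 5.03. The plan's 4.04 lies between, so this is minor.
- Six control schools: 1/3 + 1/6 = 1/4 + 1/4, so pedagogy-versus-control power matches a 4/4/4 split. Only Linear versus Non-linear suffers (2/3 against 1/2).
- Degrees of freedom: the 60% above would be 70% with a normal critical value.
- The pairwise contrasts and the conversion in step 2 account for most of the rest.

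**The case against.** The best defence has four parts.

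**The low figures are pessimistic.** The article powers changes over three time points, so the unadjusted 20% is not the planned analysis. A coefficient averaged over both follow-ups could reach 74%. The ICC of 0.16 comes from eight classes of 7-8-year-olds, and placing all of it at school level is an assumption. Schools are also matched on size and deprivation, which may reduce the relevant variance. All of this stands, and it is why a range is shown. It does not restore 90% at 218, since 86% is the ceiling even at ICC 0.

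**On the plan's own scale the loss is smaller.** Keeping f = 0.2 and 4.04, the effective numbers are 218 × 0.75/4.04 = 40.5 for 3 v 6 schools and 218 × 0.5/4.04 = 27.0 for 3 v 3. Two-group interaction power is then 79% and 59%: better, but still below 90%.

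**If all 314 children were retained, 90% can be exceeded.** It is 92% for 3 v 6 on the scale just described. In the school-level model at ICC 0 with T1 and T2 averaged, the variance is 0.0191, the SE 0.098 and the power 95%. But the plan itself allows for 20% loss at each time point, so 314 is not its analysed number.

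**The analysis plan may settle the model.** This stands. A reader might infer that the class-level wording carries into the analysis, so that school is ignored and false positives are inflated. The article does not say so. Its Data Analysis section states only that mixed models account for nesting and names no level; random-effect terms and small-sample degrees of freedom are commonly left to the analysis plan. No type I error claim is made here.

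**Conclusion.** The point holds as a power misstatement. The 90% is attached to a different test, with different degrees of freedom, from the contrasts the trial sets out to examine, and N = 54 falls short of 90% for the stated test too (81.6% with f = 0.2). At 218 analysed on 9 df, no named contrast reached 90% in any case tried.

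The result rests on a 3 + 3 split of the pedagogy schools, equal school sizes, r = 0.5, school autocorrelation of 0.8-1.0 and school ICC of 0-0.16. A 4/4/4 split leaves the pedagogy-versus-control figures unchanged.

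Two stronger readings should be resisted. The trial did not necessarily have little chance of detecting d = 0.4, since 74-86% is possible under favourable assumptions. Nor do the class-level factor or the six-school control arm explain the pedagogy-versus-control shortfall.

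**What to change.** Recompute power at school level for each of the three named contrasts, with the actual number of schools per arm and 9 df, over a stated range of school ICC and autocorrelation. Say which effect size applies to Linear versus Non-linear, and how d = 0.4 maps to the quantity tested. Replace the 90% claim with the resulting power, or with the difference detectable at 90% for each contrast. Under the assumptions above and ICC 0.16, that is about 0.5-1.2 SD for pedagogy versus control and 0.6-1.35 SD for Linear versus Non-linear. If the interaction calculation is kept for the record, correct its 54 or its 90%.

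The cost is one rewritten paragraph and a much less favourable stated power. No extra schools are needed. By the article's dates, data collection ended before publication, so the change affects how results are read, not how the trial is run.

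### The base sample of 54 children is not reproduced as a 90% power figure from the stated inputs; either the power or the effect size is misstated

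*Protocol article*

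**What the plan says.** The Protocol article, section Sample Size and Statistical Power, sets out the whole chain in one paragraph.

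- Effect: "we anticipate a small to medium effect size of *d* = 0.4 for changes in movement competence".
- Test and target: "The power calculation to detect within-between interactions for three groups and across three time points with 90% power", with "α levels set at *p* < 0.05" and a correlation of 0.5 between repeated measures.
- Result: these inputs "suggested a minimal sample size of 54 children".
- Clustering: a factor of 1 + (20 - 1) × 0.16 = 4.04 is applied. "The final power calculation including the correction factor indicated sample size of 218 children".
- Dropout: an allowance of 20% at each time point raises the target to at least 314.

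The section gives the effect only as d. It does not state the f value, the scale on which f was entered, or a nonsphericity correction.

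**The concern.** A repeated-measures interaction test is powered on f or a related quantity, not on d, so a conversion has to be made. Under the usual conversion, 54 falls well short of 90% power. The figure of 54 is the base of the chain: 218 is 54 multiplied by the clustering factor, and 314 is 218 inflated for dropout. If the base does not carry 90%, neither does the 218 to which the plan ties its power claim.

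This is the article's only power justification, and it concerns movement competence, the primary outcome. A reader of a null result would take the risk of missing an effect of d = 0.4 to be 10%. On the usual conversion it is about 18%.

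**Working it through.** **Inputs from the section:** d = 0.4; k = 3 groups; m = 3 time points; r = 0.5; alpha = 0.05; target power 90%; clustering factor 4.04.

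**Assumed, because not stated:** f = d/2 = 0.2, and sphericity (epsilon = 1, the most favourable value).

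**Method:** noncentral F for the within-between interaction.

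- λ = f² × N × m / (1 - r) = 0.04 × N × 3 / 0.5 = 0.24 N
- df1 = (k - 1)(m - 1) = 4
- df2 = (N - k)(m - 1) = 2(N - 3)

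**Step 1. The plan's own figure.** At N = 54, λ = 12.96 with 4 and 102 df. Power is 81.6%, not 90%.

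| N | Power at f = 0.2 |
|---|---|
| 51 | 78.9% |
| 53 | 80.7% |
| 54 | 81.6% |
| 66 | 89.7% |
| 67 | 90.2% |
| 69 | 91.1% |

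So 90% needs 67 children, or 69 in three equal groups. The smallest N for 80% is 53, which becomes 54 in equal groups.

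**Step 2. Sensitivity to the assumptions, at N = 54.** With three groups, d taken as the gap between the extreme groups does not fix a single f.

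| Assumption | Power at 54 | Equal-group N for 90% |
|---|---|---|
| f = 0.4 × √(1/6) = 0.163 (third group midway) | 62.0% | 99 |
| f = 0.4 × √2/3 = 0.189 (third group at one extreme) | 76.2% | 75 |
| f = 0.2, epsilon 0.75 | 72.4% | 84 |
| f = 0.2, epsilon 0.5 | 59.2% | 111 |

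Each of these lowers power, so f = 0.2 with sphericity is the favourable case among them.

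**Step 3. Can 0.4 give 54 at 90% by another entry?**

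- Entered directly as f on the standard scale, 0.4 needs only 21 in equal groups (93.9%; 18 gives 88.6%). That is not 54.
- Entered as f(U) on the partial-eta-squared scale, λ = f(U)² × (N - 3) × 2. At N = 54 this is 0.16 × 51 × 2 = 16.32, and power is 90.4%; N = 53 gives 89.7%. Here 54 is exactly the 90% answer.

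The f(U) entry does not match the stated inputs, for two reasons. It makes no use of r, which the section lists. It is also a larger effect than d = 0.4: at f = 0.2, f(U) = √(12.96/102) = 0.356, or √0.12 = 0.346 for large N, so about 0.35. Conversely, λ = 16.32 at N = 54 corresponds to f = √(16.32/324) = 0.224, which is d of about 0.45 under f = d/2.

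**Step 4. Changes to other stated inputs.** A two-group interaction gives 89.8% at 54, alpha 0.10 gives 89.0%, and r = 0.6 gives 90.1%. Each contradicts an input that the section states.

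**Step 5. Carry-through.** 54 × 4.04 = 218.2, the stated 218; 218 × 1.2 × 1.2 = 313.9, the stated 314. In reverse, 218/4.04 = 54.0, so 218 analysed children again give 81.6% at f = 0.2. Starting from 69: 69 × 4.04 = 278.8, so 279; with the plan's own dropout multiplier, 279 × 1.44 = 401.8, so about 402.

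**The case against.** The strongest reply is that everything turns on a conversion the article does not state. It gives d and never f, d does not determine f with three groups, and a condensed article may leave the entered value to a fuller protocol. At f = 0.225, 54 children would give 90.5%. This stands in part: 81.6% is the power under one assumption, not the trial's actual power. It does not rescue the statement. The two three-group conversions give less power than f = d/2, and f = 0.225 would correspond to d = 0.45 under that rule. The inputs as printed do not lead to 54 at 90%.

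A reader might also infer that the authors ran the calculation at 80% and reported 90%. The documents do not support that as fact. The f(U) entry gives 54 at the very power level the article states, without rounding to equal groups, so it explains the number at least as well. For the same reason it would be wrong to say that no reading of 0.4 yields 54 at 90%.

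A third reply is that 314 children would be enough: 314/4.04 = 77.7, which gives 94.4% at f = 0.2. That holds only if no child is lost, whereas the plan adds those children to cover dropout. Its power claim belongs to 218.

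**Conclusion.** The point holds in a limited form: 54 is not reproduced as a 90% figure from the section's own inputs. Under f = d/2 = 0.2 and sphericity it gives about 82%, against 67 children (69 in equal groups) for 90%. Under other three-group conversions it gives about 62% to 76%. Either the power is overstated for d = 0.4, or the effect with 90% power is larger than d = 0.4. The documents do not show which. The discrepancy passes unchanged into 218 and from there into 314.

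A reader might also combine this with the dropout step, which multiplies by 1.44 where dividing by 0.64 would be expected, and quote a larger shortfall. That is a separate matter and is not part of the size given here.

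**What to change.** State the effect-size metric and the value entered (f or f(U), and how it was derived from d = 0.4), rerun the calculation, and correct the sentence.

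- If f = 0.2 was intended, either restate power as about 80% for 54 and 218, or keep 90% and give 69 and 279 (about 402 with the plan's own × 1.44 dropout step).
- If f(U) = 0.4 was entered, restate the effect that the trial has 90% power to detect, and remove r = 0.5 from the inputs of that calculation, since it was not used.

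Restating the power or the effect size costs one or two sentences and no additional children. Keeping both 90% power and d = 0.4 would raise the analysed sample from 218 to 279, which is 61 more children, before dropout.

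### The target of 314 children does not cover 20% dropout at each of two follow-ups: it leaves about 201 at T2, below the plan's own 218; the matching target is 341

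*Protocol article*

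**What the plan says.** Under Sample Size and Statistical Power, the protocol article builds its number in three steps.

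- **Unadjusted size.** The calculation is for "within-between interactions for three groups and across three time points with 90% power". It "suggested a minimal sample size of 54 children".
- **Clustering.** "Assuming an average class size of about 20 participants and an ICC for movement competence of 0.16", the correction factor is 4.04. The result is given as: "The final power calculation including the correction factor indicated sample size of 218 children".
- **Dropout.** "Allowing for 20% dropout at each time points", "the aim of this study will be to have a sample of at least 314 children".

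The Design section gives one baseline (T0) and two later measurements (T1 after the intervention, T2 six months after it ends). Dropout can therefore occur at two points. No formula for the dropout step is printed.

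**The concern.** To still have a required number after a proportion d is lost, that number is divided by (1 − d). Multiplying by (1 + d) gives too few, and the gap grows when the step is repeated. The step from 218 to 314 matches multiplication by 1.2 twice.

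If so, the recruitment target does not deliver the requirement derived just before it, under the dropout rate stated beside it. The gap falls on T2, which carries the medium-term effect named under Data Analysis and the third wave of the interaction used for the power calculation. The article gives no other recruitment figure, so 314 is the benchmark a reader would use to judge whether the trial reached its planned size.

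**Working it through.** **Inputs, all from Sample Size and Statistical Power unless noted:** unadjusted size 54; class size m = 20; ICC = 0.16; cluster-adjusted size 218; dropout 20% per time point; target 314. Number of follow-ups = 2 (Design section).

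**1. Reproduce the plan's figures.**
- Correction factor: 1 + (20 − 1) × 0.16 = 4.04.
- Cluster-adjusted size: 54 × 4.04 = 218.16, giving 218.
- Target: 218 × 1.2 × 1.2 = 313.92, giving 314.

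Other routes from 218 do not give 314: 218 / 0.8 = 272.5; 218 × 1.2 = 261.6; 218 × 1.4 = 305.2; 218 / 0.6 = 363.3; 218 / 0.8² = 340.6. The double multiplication is an inference, but it is the only one of these that matches.

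**2. What 314 yields at the stated dropout.**
- T1: 314 × 0.8 = 251.2, about 251, above 218.
- T2: 314 × 0.8² = 200.96, about 201. Shortfall 218 − 201 = 17, and 17 / 218 = 7.8%.

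This does not depend on how 314 was obtained.

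**3. What the stated dropout requires.**
- 218 / 0.8² = 340.6, giving 341. Check: 341 × 0.64 = 218.2.
- Conversely, 314 tolerates a cumulative loss of 1 − 218/314 = 30.6%, or 1 − √(218/314) = 16.7% per wave. Two 20% losses make 36%.

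**4. Effect on power.** The article gives d = 0.4 but not the effect size f of the F test. To isolate the dropout step, I chose f so that 54 children give exactly the stated 90%. The test is the three-group by three-time interaction with r = 0.5: noncentrality f² × N × 3 / (1 − 0.5), degrees of freedom 4 and 2(N − 3). This gives f ≈ 0.223. N is the effective number, that is children divided by the correction factor.

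| Assumption for 201 children | Mean class size | Factor | Effective N | Power |
|---|---|---|---|---|
| Factor held at 4.04 | 20 | 4.04 | 201 / 4.04 = 49.8 | 87.0% |
| 20 is the analysed class size; same 218 / 20 = 10.9 classes | 201 / 10.9 = 18.4 | 1 + 17.4 × 0.16 = 3.79 | 201 / 3.79 = 53.0 | 89.4% |
| 20 is the enrolled class size | 20 × 0.64 = 12.8 | 1 + 11.8 × 0.16 = 2.89 | 201 / 2.89 = 69.6 | no loss (69.6 exceeds 54) |

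**The case against.** Several points on the other side stand.

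- **Only T2 is short.** At T1 the target leaves 251, above 218. The planned linear mixed models can use children with partial follow-up, so the analysed sample need not be the 201 with complete data.
- **Losing individual children shrinks classes.** The correction factor depends on m, so it falls as children drop out. Holding it at 4.04 amounts to losing whole classes. The article does not say whether 20 per class means enrolled or analysed children.
- **The target is a floor.** It is worded as a minimum, and data collection was scheduled for 2018 to early 2019, before publication in 2020. A corrected figure cannot change recruitment.

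None of this reconciles 314 with 218 at 20% per wave. The plan fixes 4.04, reaches 218 and only then adds dropout, so 218 is its stated requirement after losses. Reading the 20% as a share of the original sample at each follow-up makes matters worse: 314 × 0.6 = 188. A single 20% loss in total would leave 251, but the wording applies the loss at each time point.

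A reader might infer a larger cost: taking f = d/2 = 0.2 and keeping the factor at 4.04, power falls from 81.6% to 77.7%. The documents do not support presenting that as the cost of the dropout step. They do not state f = 0.2. The starting value of 81.6% already disagrees with the stated 90%, which is a separate question about the 54. The factor would also have to stay fixed while classes shrink; with the factor updated as in the second row of the table, the same f gives about 80.8%.

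**Conclusion.** The point holds as an arithmetic inconsistency within one paragraph. At the stated dropout, 314 gives about 201 children at T2, 17 (8%) below the plan's 218, and the matching target is 341. This needs only the printed figures and two follow-ups.

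The effect on power is small: from the stated 90% to about 87% at worst, about 89% if the correction factor follows class size, and none if 20 is the enrolled class size. Those values rest on an f calibrated to the plan's own 54 and 90%, and on 201 being the number analysed. It would go too far to infer that the trial as a whole is underpowered because of this step: T1 is adequately covered, and no estimand or analysis method depends on the figure. It is a minor correction of a sample-size figure that is wrong as written.

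**What to change.** Make one of two changes in Sample Size and Statistical Power:

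1. Correct the dropout-adjusted figure to 341 and show the step (218 / 0.8²).
2. Keep 314 and state that at 20% loss per wave it yields about 251 children at T1 and 201 at T2, or equivalently that it tolerates about 16.7% loss per wave. Give the power that 201 supports, with the effect size f and the meaning of 20 per class (enrolled or analysed) stated.

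Either takes a sentence or two. As data collection was scheduled to finish before publication, the second fits more naturally. It needs no extra recruitment, and its only cost is a slightly less favourable power statement at T2.
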